# Impact of Tai Chi Therapy on Fatigue and Cognitive Function in Individuals With Chronic Fatigue Syndrome: Protocol for a Pilot Randomized Controlled Trial

**DOI:** 10.2196/65958

**Published:** 2025-04-25

**Keywords:** Tai Chi, chronic fatigue syndrome, cognitive impairment, ANT, N-Back, fatigue, cognitive function, cognitive, protocol, protocols, randomized controlled trial, RCT, controlled trial, controlled trials, psychosomatic disorder, cognition, therapy, efficacy, safety, CFS, intervention, data analysis

## Abstract

**Background:**

Chronic fatigue syndrome (CFS) is a psychosomatic disorder characterized by persistent fatigue, primarily involving physical and mental exhaustion, with greater emphasis on the latter. This leads to a deterioration in concentration and memory. These symptoms affect cognitive functions, including attention and memory, to varying degrees. Previous research has shown that Tai Chi can help reduce fatigue in individuals with CFS. However, the relationship between alleviating CFS-related fatigue through Tai Chi and its impact on cognitive functions remains unclear. The effects of Tai Chi on cognitive functions in individuals with CFS have not been clinically validated, and its efficacy and safety have yet to be examined through large-scale randomized controlled trials. Therefore, this protocol outlines a pilot randomized, parallel, single-blind clinical trial designed to evaluate the impact of Tai Chi therapy on fatigue and cognitive functions in individuals with CFS, using both subjective and objective assessments.

**Objective:**

This pilot study aims to explore the preliminary efficacy and safety of Tai Chi in reducing fatigue and improving cognitive function in patients with CFS, and to generate data to inform future large-scale trials.

**Methods:**

We will conduct a randomized, analyst-blinded, parallel-controlled trial with a 12-week intervention period and a 4-week follow-up. Enrolled patients will be randomly assigned to either the Tai Chi group (30 patients) or the health education group (30 patients). The Tai Chi group will receive the 24-style simplified Tai Chi intervention, while the control group will receive a health education intervention. Following the 12-week intervention, a 4-week follow-up will be conducted. The Tai Chi group will train 3 times per week, consisting of 2 in-person sessions at the Physical Education Center of Shanghai University of Traditional Chinese Medicine and 1 self-directed session guided online by an instructor. The primary outcome measure is the 20-item Multi-Dimensional Fatigue Inventory (MFI-20). The secondary outcome measures include the Montreal Cognitive Assessment (MoCA), Pittsburgh Sleep Quality Index (PSQI), Attention Network Test (ANT), working memory performance (N-Back task), and magnetic resonance imaging.

**Results:**

The research protocol and informed consent form were approved by the Shanghai Clinical Research Ethics Committee on March 18, 2024 (approval number SECCR2024-22-01). Participant recruitment began in April 2024. All interventions and concurrent data collection will be completed by October 2025, and the 4-week postintervention follow-up assessments will be finalized by the end of October 2025. Data management is still ongoing; therefore, data analysis has not yet been performed.

**Conclusions:**

As a pilot trial, the findings of this study will provide preliminary clinical evidence on the role of Tai Chi in improving cognitive function in patients with CFS and will serve as a foundation for designing future large-scale trials.

**Trial Registration:**

China Clinical Trials Registry ChiCTR2400082268; https://tinyurl.com/2tkr7j7x

**International Registered Report Identifier (IRRID):**

DERR1-10.2196/65958

## Introduction

Chronic fatigue syndrome (CFS), also known as myalgic encephalomyelitis, is a complex chronic disease characterized by pathological fatigue, generalized weakness, immune dysfunction, poor sleep, pain, and cognitive impairments [1]. Its defining feature is persistent or recurrent debilitating fatigue that is not alleviated by rest and occurs despite the absence of significant abnormalities on physical examination or laboratory tests. This condition can severely affect the work and daily life of affected individuals. The etiology and pathogenesis of CFS remain unclear; however, it is generally associated with viral infections, stress, and immune, psychological, social, and genetic factors. Furthermore, it is considered part of a group of systemic diseases caused by multisystem dysregulation [2]. In recent years, with rapid societal development, the accelerating pace of life, and increasing life pressures, many people have been in a prolonged state of excessive physical and mental fatigue. Therefore, CFS is a disease with distinct contemporary characteristics. It is prevalent among individuals in a subhealthy state across various sectors, particularly those with higher education levels, those primarily engaged in mental work, and those under high psychological stress—such as office, technology, and medical professionals. The global prevalence rate of CFS is 0.8%-3.3% [3], with a rising trend annually [4], especially among middle-aged and young populations [5]. The incidence of chronic fatigue and cognitive symptoms is substantial. Long-term, recurrent fatigue can significantly reduce quality of life and may even lead to functional disability. Patients with CFS are often forced to reduce their daily activities by as much as 50%. Furthermore, 87%-95% of patients experience nonrestorative sleep and related daytime dysfunctions [6]. Thus, CFS is considered one of the most serious public health challenges globally.

CFS can be categorized as a psychosomatic disease, primarily characterized by physical and mental fatigue, with the latter being more pronounced. It often manifests as difficulties in concentration and memory. These symptoms affect cognitive functions—such as attention and memory—to varying degrees. Cognitive impairment is the most common symptom among patients with CFS and has the greatest impact on daily functioning and learning abilities [7]. In 2021, the UK’s National Institute for Health and Clinical Excellence (NICE) included cognitive impairment (brain fog) as 1 of the 4 core symptoms of CFS. Several meta-analyses conducted in other countries have shown that patients with CFS commonly experience cognitive impairment, including dysfunctions in attention, memory, and information processing [8-10]. Approximately 89% of patients with CFS present with cognitive impairments, such as memory decline and difficulty concentrating [11]. Yongjie and colleagues [12] found that among the comorbidities of CFS, memory decline and attention deficits were the most prominent, affecting over 90% of cases. Patients with CFS exhibit impairments in immediate memory, delayed memory, and attention, with attention impairment being the most severe [13]. Some scholars believe that cognitive impairment is the most severe symptom in patients with CFS. Therefore, clinicians should remain vigilant for the development of cognitive symptoms and intervene promptly. The mechanism underlying cognitive functional impairments in patients with CFS is extremely complex and not yet fully understood. Increasing evidence suggests that disruptions to normal brain function may underlie the core symptoms of CFS, including fatigue, pain, sleep disturbances, and cognitive issues [14,15].

Currently, the etiology and mechanisms of CFS remain unclear. Diagnostic criteria are still not standardized, and highly reliable treatment methods are lacking. There are no specific diagnostic or therapeutic approaches for CFS worldwide, and most treatments remain symptomatic. Modern medicine primarily focuses on symptom management through approaches such as antianxiety therapy, immune regulation, and nutritional supplementation—aimed at alleviation rather than cure. However, the efficacy of these treatments remains controversial [16]. Moreover, they are often costly and may lead to adverse reactions such as gastrointestinal dysfunction, as well as liver and kidney damage. Patients undergoing these therapies are also at risk of relapse after discontinuing treatment. Therefore, there is an urgent need for safe and effective treatment options for CFS. In recent years, exercise therapy has emerged as a research hot spot in CFS treatment, showing notable benefits in symptom improvement. Traditional Qigong, in particular, offers several advantages, including the regulation of the body, breath, and mind. Previous studies [17,18] have shown that Qigong can relieve both overall fatigue and psychological fatigue, making it an effective treatment for CFS. As a mind-body exercise with traditional Chinese cultural roots, Tai Chi holds a unique position in alternative and traditional medicine. It engages a wide range of muscle groups, including those in the legs, trunk, and arms, and requires high levels of attention and memory. Clinical studies have shown that, compared with general aerobic exercises, Tai Chi can improve or delay the decline of overall cognitive functions, including memory, attention, and executive functions, in healthy older individuals [19,20]. It has also shown benefits in those with mild cognitive impairment [19,20], as well as in individuals with Parkinson disease [21], Alzheimer disease [22], multiple sclerosis [23], and cardiovascular diseases [24]. However, the impact of Tai Chi on cognitive functions in CFS has not yet been clinically validated, and its efficacy and safety have not been assessed in large-scale randomized controlled trials.

Regular Tai Chi practice is beneficial for relieving fatigue and improving cognition in CFS, and it is more effective than general aerobic exercise. To assess the clinical effects of Tai Chi on fatigue relief and cognitive function improvement, this study aims to design a randomized, parallel, single-blind clinical trial. The purpose of this study is to examine the effects of Tai Chi therapy on fatigue and cognitive function in CFS through both subjective and objective assessments, thereby exploring the potential links between fatigue, cognitive function, and the treatment process in CFS. This trial is currently underway, and the data will be shared through scientific publications.

## Methods

### Research Design

We designed a randomized, evaluator- and statistician-blinded, parallel-controlled trial to be conducted at Shanghai University of Traditional Chinese Medicine and The Affiliated Yueyang Hospital of Integrated Traditional Chinese and Western Medicine. Participants will be randomly allocated to either the Tai Chi group or the health education group. The Tai Chi group will receive Tai Chi intervention, while the health education group will receive cognitive behavioral therapy (CBT) intervention. The total study duration is 17 weeks: a 1-week screening period, a 12-week treatment period, and a 4-week follow-up period. The protocol version issue date is March 13, 2024. Figure 1 shows the study flowchart (see Multimedia Appendix 1 for the SPIRIT [Standard Protocol Items: Recommendations for Interventional Trials] checklist).

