#### Health Education Group

Before treatment, participants will receive information related to CFS and CBT to help them understand the principles and role of cognitive therapy in CFS treatment. The health education group will receive daily health education via a WeChat group or WeChat public account. Experts in the field will be invited to give a weekly 1-hour lecture or psychological counseling session on CFS prevention and treatment. If participants are unable to attend, lecture videos will be distributed to those who missed the session. After each learning session, a practice log will be provided, and participants will be required to fill it out. The entire treatment process lasts for 12 weeks. CBT is a psychological treatment method that combines behavioral therapy and cognitive therapy.

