#### Comparator Justification

CBT was chosen as the control condition in this study based on its established role as a standard evidence-based treatment for CFS. According to the NICE guideline NG206 [27], CBT is recommended as one of the management approaches for individuals with myalgic encephalomyelitis/CFS, particularly to help them cope with the impact of symptoms and improve function. Moreover, CBT has been widely used as a comparator intervention in previous randomized controlled trials evaluating alternative or complementary treatments for CFS. Notable examples include the PACE trial, which compared CBT, graded exercise therapy, and adaptive pacing therapy, as well as other randomized controlled trials that assessed the relative effectiveness of novel interventions against CBT [28,29]. Therefore, selecting CBT as the control group in this study is methodologically appropriate and allows for a direct comparison with an established therapeutic modality.

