## Discussion

To the best of our knowledge, this study is the first to explore the effects of Tai Chi on CFS from a cognitive functional perspective. To validate the specific role of Tai Chi in CFS treatment, this study aims to evaluate the impact of Tai Chi on fatigue, cognitive functions, and changes in brain function using different clinical scales, psychological experimental paradigms, and neuroimaging scans. Currently, it is widely accepted in the academic community that CFS can cause cognitive impairments. However, some reports occasionally yield inconsistent results [34,35], possibly because early mild cognitive impairments may not be fully detected by conventional neuropsychological scales and can easily be overshadowed by other clinical symptoms. In most studies, subitems measuring cognitive functions, such as attention and memory, are typically included in the composite scores of scales for other cognitive domains or in overall cognitive assessment paradigms. Moreover, due to the strong subjectivity of scale assessments and the low sensitivity of indicators, there are certain limitations. With the use of various cognitive tasks and different methods of assessing cognitive functions, direct comparisons are not feasible, leaving a lack of more direct evidence for assessing cognitive functions in patients with CFS. Therefore, there is an urgent need to apply more precise and scientific neuropsychological experimental paradigms to assess specific cognitive domains, providing objective and accurate data to support the assessment of cognitive impairments in CFS.

Togo [36] showed that the ANT has clinical value for assessing the cognitive functions of patients with CFS. Some scholars have proposed using continuous attention assessment as a reliable biomarker for diagnosing CFS [37]. Nevertheless, there is still a lack of comprehensive ANT paradigm evaluations and analyses of attention network functions in patients with CFS. The N-Back test is a commonly used paradigm in cognitive psychology for assessing working memory capacity [38], and the N-Back task paradigm, a continuous processing operation task, is one of the most widely used experimental paradigms in working memory brain imaging studies.

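### The control arm is named and justified as CBT but described as health education, so a group difference cannot be reported as Tai Chi versus CBT

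*Protocol article*

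**What the plan says.** Four places in the protocol article define the comparator, and they do not agree.

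- **Research Design:** "while the health education group will receive cognitive behavioral therapy (CBT) intervention".
- **Comparator Justification:** the whole section defends CBT as the control, on the ground that it is an accepted treatment for CFS and has served as comparator in other trials. It ends with the claim that the choice "allows for a direct comparison with an established therapeutic modality".
- **Abstract, Methods:** "while the control group will receive a health education intervention", with no mention of CBT.
- **Health Education Group:** this is the only account of content. "Before treatment, participants will receive information related to CFS and CBT to help them understand the principles and role of cognitive therapy in CFS treatment." Then: "The health education group will receive daily health education via a WeChat group or WeChat public account." Then: "Experts in the field will be invited to give a weekly 1-hour lecture or psychological counseling session on CFS prevention and treatment." For absentees: "If participants are unable to attend, lecture videos will be distributed to those who missed the session." The section ends with a one-sentence definition of CBT.

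On interpretation, the Discussion opens with the aim "To validate the specific role of Tai Chi in CFS treatment".

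**The concern.** The comparator fixes the question that the trial answers. Being told about a therapy, hearing lectures and receiving daily educational messages is a different control condition from being treated with that therapy. If the Health Education Group section is accurate, a favourable result reported in the terms of Comparator Justification would tell readers that Tai Chi had outperformed a recognised treatment, when no such comparison was made. The article says its findings will inform larger multicentre trials, so a mislabelled comparator could carry over into their design.

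A second, lesser matter concerns attribution. The two arms are scheduled for different amounts of session time. Participants know their allocation (Blinding), and the primary outcome, the MFI-20, is listed among the self-assessment scales (Outcome Measure Assessment). Attention, supervision and expectation could therefore contribute to any difference.

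**Working it through.** **Step 1: what each place says the control arm is.**

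| Place | Comparator |
|---|---|
| Abstract, Methods | Health education |
| Research Design | CBT |
| Health Education Group | Introductory information on CFS and CBT; daily WeChat education; weekly hour of lecture or counselling |
| Comparator Justification | CBT, as an accepted treatment |

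The content in the third row mentions CBT twice: as the subject of pre-treatment information, and in a closing definition. The weekly hour may be counselling, so some psychological content is possible, but it is not specified as CBT and may equally be a lecture. No element of the schedule is described as a CBT session. The inference in Comparator Justification needs a control arm treated with CBT, and the described arm does not supply one.

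**Step 2: scheduled session time.** The article states no figure for contact time, so there is none to reproduce. Inputs are from Tai Chi Group (3 sessions a week, 60 min each, 12 weeks) and Health Education Group (1 hour a week, 12 weeks).

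- Tai Chi: 3 × 60 = 180 min a week; 180 × 12 / 60 = 36 h.
- Control: 1 × 60 = 60 min a week; 60 × 12 / 60 = 12 h.
- Control to Tai Chi: 12 / 36 = 0.33.

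**Step 3: how far that ratio depends on what is counted.**

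- Only the two in-person Tai Chi sessions: 60 / 120 = 0.50.
- All three sessions, using the itemised parts (5 + 10 + 30 + 5 = 50 min): 60 / 150 = 0.40.
- Daily WeChat education counted at m minutes a day, against 180 min: (60 + 7m) / 180. The article gives no value of m, so these are assumptions: m = 5 gives 95 / 180 = 0.53; m = 10 gives 130 / 180 = 0.72; m = 15 gives 165 / 180 = 0.92. Parity needs 7m = 120, or about 17 min a day.

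The 3:1 imbalance therefore holds for scheduled sessions only. Total contact in the control arm cannot be computed from the article.

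**Step 4: does renaming the comparator alter the sample size?** The stated figure reproduces from its own inputs (Sample Size Calculation). Pooled SD = √((2.11² + 3.29²) / 2) = 2.764; d = (7.13 − 4.80) / 2.764 = 0.843. A two-sided t test at α = .05 and power 0.80 needs 23.09 per group, rounded up to 24; 24 / (1 − 0.20) = 30. None of these inputs depends on what the control arm is called.

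**The case against.** The strongest reply is that a journal article condenses the full protocol. Therapist, manual and session content are details commonly left out, and the section does include orientation to CBT, possible counselling and a definition of the therapy. This stands in part. The article shows a contradiction but does not settle which side is true, so a reader who concludes that CBT is certainly not delivered goes further than the text allows. It does not remove the contradiction, because both accounts are stated text and the claim of a direct comparison is an affirmative one.

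Three further inferences are tempting and not supported:

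- *That controls receive a third of the contact time.* This sets the daily WeChat education to zero while counting in full the Tai Chi self-practice hour, which is itself supervised through WeChat. Only a third of scheduled session time can be defended.
- *That unequal contact is a flaw in the plan.* Nowhere does the article claim matched contact, and comparing two programmes as delivered is a legitimate design. The Discussion phrase about a specific role is loose wording; the stated objective is preliminary efficacy and safety.
- *That the whole between-group conclusion fails.* Randomisation still supports a contrast between the programmes delivered. The Abstract's conclusions and the closing paragraphs of the Discussion do not claim superiority to CBT as a trial result, and the Discussion asks that findings be read with caution.

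**Conclusion.** The point holds as a contradiction about the identity of the comparator, together with one inference that the described arm cannot support. If the Health Education Group section is accurate, the trial compares a Tai Chi programme with a health education programme, and no result can be reported as Tai Chi versus CBT. What is affected is the name of the comparator, the direct-comparison claim and the wording of the conclusion; the randomised contrast, sample size and analysis are not.

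The difference in scheduled sessions (36 h against 12 h, excluding WeChat education of unknown length) is a limit on interpretation. With unblinded participants and a self-reported primary outcome, a difference cannot be credited to something specific to Tai Chi.

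The verdict takes the article's description of the control arm at face value. A full protocol specifying a CBT course would reverse which passages need correcting, but would not remove the need to correct them.

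**What to change.** Reconcile the Abstract, Research Design, Health Education Group and Comparator Justification so that they describe one comparator.

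- If the Health Education Group section is what is delivered: call the comparator health education, with CBT information and a weekly lecture or counselling session, everywhere. Delete the direct-comparison claim from Comparator Justification. Limit the conclusion to the Tai Chi programme versus that health education programme.
- If a CBT course is in fact delivered: correct the Abstract and the Health Education Group section to say so.

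In either case, add to the limitations that scheduled session time is unequal, with the figures and the exclusion given above, and that a difference is not evidence of a Tai Chi-specific effect. Report session attendance by arm where the practice logs allow; the article does not say whether they record attendance or duration.

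The cost is a weaker claim, some rewording and perhaps one descriptive table. The Results section says that statistical analysis has not yet been performed, so the correction can precede any result.

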**Figure 1 figure1:**
[figure not shown]
Flow diagram of the study design. ANT: Attention Network Test; CBT: cognitive behavioral therapy; MFI-20: 20-item Multi-Dimensional Fatigue Inventory; MoCA: Montreal Cognitive Assessment; TJQ: Tai Ji Quan (Tai Chi).

